### Effectiveness trial methodology

A two-arm cluster randomized controlled parallel trial is being conducted with the general practice as the unit of randomization and outcomes measured at both practice change and patient outcome levels. Cluster randomization is used in order to avoid contamination among patients of the same GP because the intervention is delivered by the GP. Randomizing GPs within the same practice to the same arm likewise avoids contamination among GPs. The trial is being conducted according to CONSORT guidelines [32]. Figure 1 provides a flow chart of participants through the cluster trial, and Table 2 summarizes the research questions and measurements. Recruitment commenced in June 2015.

**Fig. 1 Fig1:**
[figure not shown]
Flow of participants though cluster randomized trial

**Table 2 Tab2:** Research questions and evaluation

Study outcomes	Research questions	Measurement
Effectiveness	Will iSOLVE be effective in reducing falls in patients of participating practices compared to control practices?	Falls over 12 months—recorded daily on monthly calendars
	Will iSOLVE increase general practitioners’ engagement in fall prevention management and referral practices compared to the control GPs?	Pre-post survey of GPs in trial—management of fall prevention and any changes in practice (Q11: frequency of risk factor assessment, medication review, advice); referral patterns (Q12: frequency of referral and to whom); knowledge of fall prevention services.
	Will iSOLVE be effective in reducing burden of drug risk and polypharmacy in use of drugs associated with falls in patients of participating practices compared to control practices?	Drug Burden Index; Falls Risk Increasing Drugs (FRID); Changes in polypharmacy and in use of drugs associated with falls (e.g., psychotropics).
	Will iSOLVE be cost effective from a healthcare funder perspective, and expressed as an incremental cost per fall avoided?	Falls and Health care utilization—monthly calendars intervention costs—staff, training, capital costs, consumables.
	Will patients in the intervention group report significantly higher interaction with their GP about fall prevention and engagement in fall prevention activities compared to the control group?	Pre-post patient survey.
Implementation	How are the iSOLVE strategies adopted (or not) by general practitioners (GPs), by Allied health professional’s (AHP)), and by the primary care network? How does this change practice in fall prevention? How does this influence the nature of pathways for identifying older people at risk and managing fall risk within primary care?	In-depth interviews with a sample of the participating trial GPs, AHPs participating in the workshops and with key coordinating stakeholders, such as Primary Care Network staff
	What are the factors that facilitate embedding of the intervention in usual care?	In-depth interviews as above Meeting minutes, observations, and field notes. AHP planning strategies document from the workshops.
	What factors will influence sustainability of training and knowledge translation for GPs, AHPs and community pharmacist?	In-depth interviews of GPs and AHPs as above Pre- and post surveys of AHPs who participate in the workshops AHP planning strategies document from the workshops
	What is the GPs professional network in relation to fall prevention and who is influential within their network?	Relational network (who and influence) questions in survey for trial GPs. Network influence question in AHPs survey and in the ecological survey of GPs in geographical area of SNPHN
	How effective is iSOLVE dissemination across the SNPHN network?	Geographical survey of GPs in SNPHN

#### Eligibility criteria

Inclusion criteria for patients are being identified as having a fall in the past year or being worried about falling (verified using the short form of the Falls Efficacy Scale) and residing in the community. Exclusion criteria are being unable to understand the study information, an unstable medical condition, severe physical disability, or moderate to severe dementia (measured by the short portable mental status questionnaire). Inclusion criteria for general practices are that they are within the SNPHN area.

#### Outcomes

The primary outcome is the number of falls per person in 12 months. Secondary outcomes are Drug Burden Index at the patient level and GP engagement in fall prevention management and GP referral practices. Secondary outcomes are measured using surveys at baseline and 12 months for patients and baseline, 3 and 12 months for GPs in order to compare change from baseline between groups.

#### Sample size estimate

This cluster randomized trial of 560 patients from 28 GP practices is designed to have 80% power to detect as significant at the two-sided 5% level a 15% between group differences in the proportion of participants falling, from 50% in the control group to 35% in the intervention group (30% relative reduction). We have assumed 50% will fall in the control group, based on previous trials. A reduction to 35% is feasible, as a reduction of this size was found in a previous meta-analysis [33]. Assuming a cluster size of 20 participants per GP practice, an intra-cluster correlation coefficient (ICC = 0.01) and a 15% loss of patients, we require 26 clusters with a total of 520 patients. In all, 28 GP practices (560 patients) will be recruited to allow for possible loss of whole practices during the 12-month follow-up.

#### Recruitment of GP practices

GPs are invited to participate in the study by a number of approaches: promotional flyers and information distributed via the SNHN database and a database developed by the iSOLVE team by mapping GP practices using available web resources (e.g., Google™ health engines and business directories), during SNPHN events, distributed by SNPHN primary care officers, attached to the iSOLVE annual GP area survey and opportunistic such as word of mouth. For practices with multiple GPs, once one has agreed to be part of the study, others are provided with information and invited to participate.

#### Recruitment of patients

Letters are sent from the GP to people 65 years and over from their patient database. The GPs scan the list to ensure the identified patients are not living in high-care residential or hostel accommodation, do not have an unstable medical condition, are not in palliative care and are current patients. The letter invites patients to contact the project RA by phone, email, or mail if they have had a fall in the past 12 months or are worried about falling.

#### Randomization and blinding

The randomization schedule was computer-generated by a researcher at a distant site and not involved in group allocation or data collection (JS) using random permuted blocks of size 6, 4, or 2, stratified by the number of eligible patients attending the GP practice (≤80; >80). Allocation is concealed using sequentially numbered opaque envelopes. Patient lists of eligible patients are compiled by the GP practice. The allocation of practice to group occurs after the GP baseline survey, and patient lists are generated and allocation is done by a researcher not involved in practice recruitment or data collection (LC). Practices are recruited by the project manager ([name]) who also advises them of their allocation. Another researcher who is blinded to the group allocation of the GP practices contacts individual participants to explain the study, obtains signed consent, and conducts the assessments. Baseline assessments are conducted on a home visit. Patients attending the control group practices are asked not to disclose their participation in the study to their GP.

#### Intervention

The practices randomized to the intervention will receive the iSOLVE intervention, and the practices allocated to control will continue to offer usual care. Control practices will be offered the iSOLVE academic detailing, resources and software when all their patients complete the 12-month-follow-up period.

#### Measures and data collection

Patient baseline data for control and intervention patients will include history of falls and fall injuries in the past 12 months, age, hospitalization in the past year, current medications, medication dosage and frequency, and comorbidities using the Functional Comorbidity Index [34]. Patients are asked to record falls using a prospective falls calendar to be completed on a daily basis and returned by mail monthly. Fall calendars also prompt patients to record the circumstances of a fall, whether any injuries occurred and whether any medical help was sought as a result of the fall. If a person does not return their fall calendar, they are telephoned to determine whether they have fallen. A 12-month follow-up survey ascertains patient engagement in fall prevention interventions or activities over the past year, interaction with GP about fall prevention, current medications including dosage and frequency. Medication survey questions will also generate data to determine prevalence and change over 12 months in medication exposures that have been associated with increased risk of falls with Drug Burden Index [35] as the major secondary measure. Other medication data will include polypharmacy, falls risk-increasing drugs [36, 37], and use of psychotropics (antipsychotics, antidepressants, and other mood stabilizers, benzodiazepines, and z-drugs) and other drug classes of interest.

The GPs complete a survey at baseline, 3 and 12 months, comprising a combination of open-ended and Likert scale response questions. The questions cover beliefs about fall prevention, knowledge of local fall prevention services, management of fall prevention and any changes in practice, and referral patterns.

#### Data analysis plan

Data analysis will be on an intention-to-treat basis. For the primary analysis of falls, negative binomial regression will be used to compare the total number of falls per person in the two groups, using an offset for exposure time and accounting for clustering. GP engagement in fall prevention management and GP referral practices will be assessed using questions 11 and 12, respectively, of the 12-month GP survey and corresponding questions on the baseline survey. For management, a score from 0 to 3 will be allocated to each of the first three items and summed to give a total out of 9. The total score for each GP at 12 months will be compared between groups using regression analysis with baseline score as a covariate and adjusting for clustering by GP practice. For referral practice, the number of types of practitioners (out of 13 possible) to whom a GP sometimes or often refers older patients at risk of falling will be counted. The change from baseline for each GP will be compared between groups using Poisson regression, adjusting for clustering by GP practice. Change in Drug Burden Index will be calculated for each patient and compared between groups using regression analysis, controlling for any baseline differences in risk factors (age, gender, comorbidities, hospitalization in past year, and use of walking aid) and accounting for clustering.

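### As described, the primary falls model names neither the randomisation stratum nor baseline fall history, giving up some efficiency and some protection against chance imbalance in fall history

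*Protocol article*

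**What the plan says.** All places are in the protocol article.

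- **Outcomes:** "The primary outcome is the number of falls per person in 12 months".
- **Data analysis plan:** "negative binomial regression will be used to compare the total number of falls per person in the two groups, using an offset for exposure time". Clustering is also accounted for. No covariate is named for this model, and nothing says that the model is deliberately unadjusted. For the GP management score, the same paragraph names the baseline score as a covariate. For change in Drug Burden Index it names age, gender, comorbidities, hospitalisation in the past year and walking-aid use.
- **Randomization and blinding:** practices are allocated "using random permuted blocks of size 6, 4, or 2", and allocation is "stratified by the number of eligible patients attending the GP practice", with the cut at 80.
- **Measures and data collection:** "Patient baseline data for control and intervention patients will include history of falls and fall injuries in the past 12 months".
- **Eligibility criteria:** patients qualify by "being identified as having a fall in the past year or being worried about falling", so fall history differs between patients by design.

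**The concern.** Three features meet in the primary analysis. A design factor used in randomisation is not named in the model. A baseline measure of the outcome itself, probably one of the stronger predictors of later falls, is collected but not named. The paragraph that is silent here does specify covariates for two secondary outcomes, so the primary outcome is described with less adjustment than they are.

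The stake is efficiency and robustness. Variation between patients that fall history could explain stays in the residual dispersion and widens the interval for the rate ratio. With about 14 practices per arm, the share of prior fallers can differ between arms by chance, and stratifying on practice size does not control that. If practice size predicts falls, a model without the stratum also estimates the between-practice variation as larger than the variation that affects the comparison of arms. Its standard error is then slightly too large.

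**Working it through.** **1. The plan's own figure.** Inputs from the Sample size estimate section: 50% v 35% falling, two-sided 5%, 80% power, clusters of 20, ICC 0.01, 15% loss.
- The two-proportion formula gives 170 per arm, or 183 with continuity correction.
- Design effect: 1 + (20 − 1) × 0.01 = 1.19.
- 2 × 183 × 1.19 = 435.5; 435.5 / 0.85 = 512.4; 512.4 / 20 = 25.6, so 26 clusters and 520 patients, as stated.

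The calculation takes no credit for covariates, so the planned size does not depend on them.

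**2. Analytic gain.** The documents give no dispersion, no share of prior fallers and no prognostic strength, so these inputs are assumed. Take 14 practices per arm with 17 followed patients each (20 × 0.85), so n = 238 per arm, and design effect 1 + 16 × 0.01 = 1.16. Then

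Var(log RR) = 1.16 × (1/μ0 + 1/μ1 + 2k) / n,

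where k is the dispersion, μ0 is set so that 50% of controls have no fall, and μ1 = 0.7 μ0. Covariates that explain 10 to 30% of between-patient variation reduce k by that share. For k = 1: μ0 = 1.0, Var = 1.16 × (1 + 1.429 + 2) / 238 = 0.0216, SE 0.147. With 30% explained, 2k falls to 1.4, and the variance ratio is 3.829 / 4.429 = 0.865.

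| k | μ0 | Variance cut | Power without | Power with |
|---|---|---|---|---|
| 0.5 | 0.828 | 2.5–7.6% | 0.731 | 0.742–0.765 |
| 1 | 1.0 | 4.5–13.5% | 0.680 | 0.700–0.742 |
| 2 | 1.5 | 7.1–21.4% | 0.577 | 0.609–0.681 |

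The rate ratio of 0.70 carries the planned 30% relative reduction in the proportion falling over to the rate. If μ1 is instead set so that 35% fall, the rate ratios are 0.58, 0.54 and 0.46. Power without covariates is then already 0.964 to 0.995, and the gain is at most about 1 point.

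**3. Simulation.** 28 clusters of 17, k = 1, 60% with a prior fall (yes/no), 1,500 runs per row, negative binomial model with cluster-robust SE. Each cell shows no covariates / stratum / stratum + prior fall. SD and power are at rate ratio 0.70.

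| Prior-fall RR, stratum RR | SD of log RR | Power | Type I error |
|---|---|---|---|
| 1.5, 1.0 | 0.1423 / 0.1421 / 0.1408 | 0.714 / 0.723 / 0.725 | 0.057 / 0.059 / 0.056 |
| 2, 1.0 | 0.1440 / 0.1440 / 0.1398 | 0.707 / 0.722 / 0.743 | 0.071 / 0.074 / 0.067 |
| 2, 1.25 | 0.1428 / 0.1426 / 0.1402 | 0.654 / 0.693 / 0.718 | 0.045 / 0.059 / 0.055 |
| 3, 1.25 | 0.1398 / 0.1398 / 0.1347 | 0.658 / 0.711 / 0.749 | 0.036 / 0.055 / 0.053 |

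- The mean log rate ratio under the null was about 0 in every model, so the unadjusted estimate is not biased.
- The stratum leaves the SD essentially unchanged. Its effect is on the standard error.
- Both covariates together cut the variance by 1 − (SD ratio)²: 2.1%, 5.7%, 3.6% and 7.2%.
- Power rises by 1.1, 3.6, 6.4 and 9.1 points. In the last two rows part of this is calibration, because the type I error also moves up.
- The Monte Carlo error of a 5% rate is √(0.05 × 0.95 / 1500) = 0.006. So 0.036 is clearly low, 0.045 is not, and 0.067 to 0.074 is clearly high.

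**4. Chance imbalance in prior fallers.** With 280 patients per arm in clusters of 20, the SD of the arm difference is √(2p(1 − p) × DE / 280). For p = 0.4 and ICC 0.01: √(2 × 0.24 × 1.19 / 280) = 0.045, so the 95% range is ±0.089. With a prior-fall RR of 2, an imbalance d of that size shifts the unadjusted rate ratio by (1 + p + d/2) / (1 + p − d/2) = 1.444 / 1.356 = 1.065. Over p = 0.4 to 0.8, ICC 0.01 to 0.05 and prior-fall RR 1.5 to 3, the 95% range is about ±7 to 11 percentage points, and the shift at its edge is about 3 to 13%.

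**The case against.** The strongest objection is that silence is not a decision. This is a condensed article, its analysis plan is not shown, and primary-model covariates are a routine item there. That stands in part: the text supports only that no covariate is named here. It is not a full answer, because the same paragraph does go down to covariates for two other outcomes.

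A reader might infer more than the documents support.
- *That the primary analysis is biased or invalid.* It is not. Randomisation makes the unadjusted estimate unbiased on average, and chance imbalance is part of the variation that its confidence interval covers.
- *That omitting the stratum exposes the trial to imbalance in practice size.* Permuted blocks within strata already limit that.
- *That the standard errors are wrong.* They are too wide only if practice size predicts falls, which no section states.
- *That a large, definite gain is being given up.* A separate simulation using log(prior falls + 1) gave variance cuts of 3 to 27%, equivalent to about 3 to 37% more patients. It needs a recorded count and assumed correlations of 0.14 to 0.53 between prior and later falls, and it used only 300 runs per scenario. The article mentions fall history and does not say that a count is kept.

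Adjustment also adds terms to a model with few clusters. That stands, and it bears on how the fix is written.

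**Conclusion.** The point holds as a recommended improvement, not as an error. The stated model is valid and the sample size is unaffected. Three things are lost: some efficiency, protection against chance imbalance in fall history, and correct calibration if practice size is prognostic.

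No single figure follows from the documents. Under the assumptions shown, the variance of the log rate ratio falls by roughly 2 to 20%. The yes/no simulation lies at the low end (2 to 7%), and the top needs a dispersion near 2 with covariates explaining 30% of between-patient variation. At a rate ratio of 0.70, power rises by a few points, at most about 10. If the rate effect is as strong as a drop from 50% to 35% falling implies, the power gain is 1 point or less, and narrower intervals and protection against imbalance are the remaining reasons.

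**What to change.** Prespecify, before unblinding, that the primary negative binomial model contains group, the randomisation stratum (≤80/>80 eligible patients) and baseline fall history as fixed covariates, with the exposure offset and clustering as now. Code fall history in count categories (such as 0, 1, 2 or more) if a count is recorded, otherwise as yes/no. Keep the list to these two. Name a small-sample correction suited to 28 clusters: in the simulation, uncorrected cluster-robust standard errors gave type I errors up to 0.074, with or without covariates. Report the model without covariates as a sensitivity analysis.

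The cost is one or two sentences and no new data, provided fall history is recorded as described. The downside is one or two extra terms with few clusters. Only the stratum uses up between-practice degrees of freedom, and it uses one. If the full analysis plan already specifies this, the sponsor need only say so.

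### The GP referral analysis names Poisson regression for a change score that can be negative, so response and model do not match

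*Protocol article*

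**What the plan says.** The Data analysis plan defines the referral score for each GP as "the number of types of practitioners (out of 13 possible) to whom a GP sometimes or often refers older patients at risk of falling". It is taken from one question "of the 12-month GP survey and corresponding questions on the baseline survey". The sentence after the definition fixes the analysis: "The change from baseline for each GP will be compared between groups using Poisson regression, adjusting for clustering by GP practice".

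The same paragraph treats the companion GP outcome, the management score out of 9, differently: "The total score for each GP at 12 months will be compared between groups using regression analysis with baseline score as a covariate".

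The Outcomes section lists GP referral practices as a secondary outcome and says that the secondary outcomes are surveyed repeatedly "in order to compare change from baseline between groups". The Research questions section places GP management and referral within the second of the two primary effectiveness questions.

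**The concern.** The article names both the response (each GP's change) and the model (Poisson), and the two are incompatible. It mentions no shift, baseline covariate or group-by-time term that would turn the response into a non-negative count. Because both elements are stated, this is not a detail left open for a separate analysis plan.

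At stake is the prespecified status of one named effectiveness comparison. If the stated model proves unusable or its estimate meaningless, a replacement has to be chosen after the data are in hand. That is avoidable for an outcome that belongs to a primary effectiveness question.

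**Working it through.** **Inputs from the article.** Score range 0 to 13; time points baseline and 12 months; response is the per-GP change; model is Poisson; 28 practices in two arms, so about 14 per arm. The article gives no mean, spread, correlation or number of GPs for this outcome, and no figure to reproduce. The only sizing calculation concerns the proportion of patients falling and has no bearing here.

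**Step 1: support.** Change = (12-month count) - (baseline count), so the minimum is 0 - 13 = -13 and the maximum is 13 - 0 = +13. The Poisson log-likelihood is the sum of y·log(μ) - μ - log(y!), defined for y = 0, 1, 2, … A negative y has probability zero, so a single one sends the log-likelihood to minus infinity.

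**Step 2: how often negatives would occur.** Assumptions: baseline mean 6.5 of 13, binomial margins, latent baseline-to-12-month correlation of 0, 0.5, 0.7 or 0.8.

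| Mean shift (types) | Share of GPs with negative change |
|---|---|
| 0 | 33.4% to 42.3% |
| +1 | 9.7% to 27.6% |
| +2 | 1.5% to 15.7% |
| +3 | 0.1% to 7.5% |

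Control practices continue usual care, so a shift near zero is plausible there. With one GP in each of 14 control practices, treated as independent, the chance of no negative change is (1 - 0.334)^14 = 0.0034 at best and (1 - 0.423)^14 = 0.0005 at worst.

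**Step 3: what a log-link fit returns anyway.** With only a group term, the estimating equations set each fitted mean equal to the arm's mean change. The group coefficient is therefore log(intervention mean change / control mean change), which exists only if both means are positive. One simulated set of 60 GPs (30 per arm, baseline and 12-month counts independent, true gain 0 in control and 2 in intervention) had 16 negative changes and mean changes of 0.10 and 1.633.

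- GLM, maximum-likelihood Poisson and GEE all returned an intercept of log(0.10) = -2.303 and a group coefficient of log(1.633/0.10) = 2.793. All had log-likelihood minus infinity.
- The implied ratio is 1.633/0.10 = 16.3, for a difference of 1.633 - 0.10 = 1.53 practitioner types. The true ratio, 2/0, does not exist.
- With the control changes lowered by 2 (mean 0.10 - 2 = -1.90), GLM and GEE both stopped with an error.

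**Step 4: the alternative on the same data.** A Poisson model for the 12-month count with the baseline count as covariate gave a finite log-likelihood (-126.1) and a group coefficient of 0.246. That is a ratio of exp(0.246) = 1.28, against a simulated truth of 8.5/6.5 = 1.31. A Poisson model of both counts with a group-by-time term was also well defined (log-likelihood -249.6).

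**The case against.** The strongest defence is that this is loose wording. The authors may have meant Poisson regression on the counts, with change captured through a baseline covariate or a group-by-time term; both work in Step 4. The Outcomes sentence about comparing change is compatible with that, since it also covers the management score, which is analysed with a baseline covariate. This defence bears on seriousness but does not rescue the sentence: the text makes the per-GP change the response, in contrast to its wording for the management score.

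A reader might infer that the model can never be fitted. The documents do not support that. In 300 simulated trials per scenario (60 GPs, assumed parameters), GLM and GEE gave finite estimates in about 98% to 100% of runs in which both arms' mean changes were positive, and in 92% to 98% of all runs with modest gains in both arms. With no gain in control, about half failed. Failure depends on the arm means, not on the presence of any negative value.

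A reader might also infer that Poisson standard errors would be too wide even for the raw count, because it is capped at 13. That holds only if all GPs share one referral propensity. With beta-binomial variation between GPs (mean proportion 0.3 or 0.5, concentration 3 to 12), the variance 13p(1 - p)[1 + 12/(c + 1)] runs from 5.25 to 13.0 against Poisson means of 3.9 to 6.5. The ratio of Poisson to actual standard error is then about 0.60 to 1.02, mostly too narrow; baseline adjustment would reduce the residual variance and could move it again. The article also plans to adjust for clustering, and if robust errors are used the Poisson variance does not set the standard error. No conclusion about width follows.

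Finally, nothing in the article suggests that negative changes would be discarded or set to zero, so no bias of that kind can be charged to the plan.

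**Conclusion.** The point stands as a mismatch between response and model. It follows from the definitions alone: a difference of two 0-13 counts can be negative, and a Poisson variable cannot. The claim about size is conditional. The 33% to 42% of GPs with a negative change under no shift rests on the assumed mean, binomial margins and correlations, and falls quickly as the mean gain rises. What survives any such assumption is that the stated model has no valid likelihood once one change is negative, and that its log-link estimate is a ratio of mean changes that loses meaning as the control mean change approaches zero.

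The outcome is secondary. The falls analysis, sample size, randomisation and data collection are untouched. The sentence should be corrected, and the referral comparison belongs to a primary effectiveness question, but the trial's main result does not depend on it.

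**What to change.** Replace the sentence so that each GP's 12-month referral count is compared between groups with the baseline count as covariate, accounting for clustering by practice. This mirrors the management score's "regression analysis with baseline score as a covariate and adjusting for clustering by GP practice". Name the model: linear regression (ANCOVA), or a count or binomial-type model suited to a 0-13 outcome. The choice between these is secondary to removing the change score as a Poisson response. If change over time is preferred as the estimand, a repeated-measures count model with a group-by-time term also works, provided the text says so.

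The Outcomes section needs no amendment. The cost is one sentence, ideally settled before the 12-month GP data are analysed, with no new data and no change in sample size.

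### The Drug Burden Index analysis uses change from baseline without adjusting for baseline index, and its covariate wording does not clearly fix the model

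*Protocol article*

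**What the plan says.** All references are to the protocol article, Effectiveness trial methodology.

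- **Rank.** Measures and data collection describes the medication data "with Drug Burden Index [35] as the major secondary measure".
- **Outcome form.** Data analysis plan: "Change in Drug Burden Index will be calculated for each patient and compared between groups using regression analysis".
- **Covariates.** The same sentence continues "controlling for any baseline differences in risk factors (age, gender, comorbidities, hospitalization in past year, and use of walking aid"), and adds that clustering is accounted for. Baseline Drug Burden Index is not named, and no test or threshold defines a baseline difference.
- **Comparison in the same paragraph.** The GP management score at 12 months is "compared between groups using regression analysis with baseline score as a covariate and adjusting for clustering by GP practice".
- **Data available.** Patient baseline data include "current medications, medication dosage and frequency, and comorbidities using the Functional Comorbidity Index". Under Outcomes: "Secondary outcomes are measured using surveys at baseline and 12 months for patients". Both values of the index are therefore obtainable for each patient who completes the 12-month survey.

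**The concern.** Two features of one sentence are at issue.

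First, in a regression of change that omits the baseline value, the coefficient on baseline is in effect fixed at 1. When r is below 1, patients with a high baseline tend to fall back and those with a low baseline tend to rise. The change score subtracts the whole baseline where only a fraction r of it carries forward. That costs precision, and it moves the estimate whenever the arms differ at baseline by chance. Stratification is by number of eligible patients only, so nothing in the design balances the index itself.

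Second, if covariates enter only when a difference is seen, the data decide the model. Imbalance does not identify which variables are prognostic, and without a rule two analysts could fit different models to the same data.

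What is at stake is the precision and reproducibility of the main medication result. The falls result is not involved.

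**Working it through.** **The plan's own figures.** The article gives no standard deviation, correlation, target difference or power for Drug Burden Index, so there is no figure to reproduce for this outcome. The trial's sample size does reproduce. For 50% against 35%, two-sided 5%, 80% power, with continuity correction, 183 patients per arm are needed. Then 2 x 183 x [1 + (20 - 1) x 0.01] / 0.85 = 366 x 1.19 / 0.85 = 512.4 patients, or 25.6 practices of 20, rounded up to 26 practices and 520 patients. The sample size is not in question.

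**Inputs.** From Sample size estimate: 28 practices, 560 patients, 15% loss, ICC 0.01. Assumed here: the same ICC applies to Drug Burden Index; its SD is equal at baseline and 12 months; r ranges from 0.5 to 0.9.

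**Precision.** In units of the outcome variance, Var(change) = 2(1 - r) and Var(ANCOVA) = 1 - r². The ratio ANCOVA/change is (1 - r²) / [2(1 - r)] = (1 + r)/2. Its inverse, 2/(1 + r), gives the extra patients that the change score needs for equal precision.

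**Detectable difference and power.** Analysed patients: 560 x 0.85 = 476, about 17 per practice. The design effect is 1 + 16 x 0.01 = 1.16, so the effective number per arm is 238/1.16 = 205.2. At 80% power the detectable difference is 2.80 x sqrt(2/205.2) = 0.277 SD, multiplied by sqrt[2(1 - r)] for change or sqrt(1 - r²) for ANCOVA. Where ANCOVA has 80% power, the change score has power Φ(2.80 x sqrt[(1 + r)/2] - 1.96).

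| r (assumed) | Variance saved by ANCOVA | Extra patients for change score | Detectable difference, change / ANCOVA (SD) | Power of change score when ANCOVA has 80% |
|---|---|---|---|---|
| 0.5 | 25% | 33% | 0.277 / 0.240 | 67.9% |
| 0.7 | 15% | 18% | 0.214 / 0.198 | 73.3% |
| 0.8 | 10% | 11% | 0.175 / 0.166 | 75.7% |
| 0.9 | 5% | 5% | 0.124 / 0.121 | 78.0% |

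**Shift under chance imbalance.** If the intervention arm starts d higher, the unadjusted change estimate moves by -(1 - r)d. For d = 0.1 SD this is -0.05, -0.03, -0.02 and -0.01 SD at the four values of r. The standard error of the baseline difference is sqrt(4 x 1.16/476) = 0.099 SD, so an absolute difference of 0.1 SD or more arises in about 3 trials in 10. A larger practice ICC for the index would make it commoner.

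**Simulation check.** The set-up was 28 practices of 17 analysed patients, ICC 0.01, five covariates each related to baseline index (coefficient 0.2) and to the 12-month value only through it, cluster-robust standard errors, and 4,000 runs per scenario.

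- SD of the estimate, change against ANCOVA: 0.0988 / 0.0850 (r = 0.5), 0.0763 / 0.0707 (r = 0.7), 0.0442 / 0.0431 (r = 0.9). The squared ratios are 1.35, 1.16 and 1.05, against 1.33, 1.18 and 1.05 from the formula.
- Adjusting change for all five covariates gave 0.0963 (r = 0.5) and 0.0757 (r = 0.7). In this set-up they recover little of what baseline index would give.
- Mean estimates under no effect were within 0.001 of zero for every method.

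**Openness of the covariate set.** Five optional factors allow 2⁵ = 32 models. If a difference meant p < 0.05 and the factors were independent, at least one would enter by chance with probability 1 - 0.95⁵ = 23%; at p < 0.10, 1 - 0.90⁵ = 41%. In the simulation, entry at p < 0.05 gave type I error of 0.0495, 0.0492 and 0.044 at r = 0.5, 0.7 and 0.9.

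**The case against.** The other side has several good points.

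- **The analysis is valid.** Under randomisation the change score is unbiased on average, it answers the article's stated aim of comparing change from baseline, and it is used within a covariate-adjusted, clustered regression. This stands; what remains is efficiency and the shift under a chance imbalance.
- **The covariates may be fixed after all.** The list is closed, and the sentence can mean that all five factors are always adjusted for so as to remove whatever differences exist. This stands as a possible reading. The conditional reading is the more natural one, but not the only one. Under either reading baseline index is missing.
- **An entry rule belongs in the analysis plan.** True for a threshold, and its absence alone would be no finding. But the article itself states the outcome form and the candidate covariates, and the point concerns what it states.
- **The size is unknown.** Correct: r is assumed, and for a very stable index (r about 0.9) the gain is only about 5% of variance.

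Two stronger inferences are tempting, and neither is supported. A reader might conclude that choosing covariates by imbalance invalidates the nominal error rate. Mechanical selection at p < 0.05 gave 0.044 to 0.050 in simulation, so no inflation is shown; the harm is an open model. A reader might also infer that walking-aid use is not collected because Measures and data collection does not list it. That list omits gender too and need not be exhaustive.

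**Conclusion.** The point holds as a free improvement to a secondary analysis. The article's covariate list for change in Drug Burden Index leaves out the baseline index, while the same paragraph handles the GP management score with baseline as a covariate and gives no reason for the difference. The direction of the precision loss is certain for any r below 1 under equal variances. Its size, 25% of variance down to 5% across r = 0.5 to 0.9, rests on that assumed range and on the falls ICC carrying over to this outcome. The covariate wording is ambiguous, and on its more natural reading the model is not fixed in advance. It would go too far to call the planned comparison biased or its p-value invalid. The primary falls analysis and the sample size are untouched.

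**What to change.** In Data analysis plan, regress 12-month Drug Burden Index (or its change) on group with baseline Drug Burden Index as a covariate, as is already done for the GP management score. With baseline in a linear model, the group effect is the same whether the outcome is the 12-month value or the change. Always include the five named factors, account for clustering by practice, and replace the wording that ties adjustment to baseline differences with a fixed covariate list.

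The cost is one sentence, settled before the outcome data are examined. No new data are needed, because the baseline index already has to be computed to form the change.
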